**9.4. Other rare outcomes**

While the study cannot be powered for their meaningful analysis, we will collect

a) ICU admissions, b) safety outcome of actionable hypotension (systolic blood pressure <5th percentile for age51 treated with IV fluids/other therapy) **(Section 10 Adverse and Serious Adverse Events)**. While many physicians claim to use IVMg to decrease ICU admissions, only 5% (19/372) of hospitalized children received ICU care in MAGNUM.3

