**6.5. Measures to Minimize Bias: Randomization and Blinding**

**Treatment allocation:** The leading site pharmacy will use the randomize.net tool to produce the study Master Randomization tables, stratified by site and age group (< 6years old, i.e. prior to 6th birthday vs ≥6 years old as pre-schoolers may respond differently to asthma therapies),52 employing permuted randomization of varying block sizes in a 1:1 ratio of Mg sulfate to placebo. The study nurse will transcribe the assigned study kit numbers into the secure Health Canada-validated REDCap database.

Master lists will be provided to all participating research pharmacies which will permit the preparation of the study kits according to the randomization schedule.

Version Date: June 25, 2025 (v3.0)

Page **20** of **54**

[figure not shown]

**MAGICIAN** Clinical Trial Protocol

The patients, outcome assessors (study nurses, ED physicians) and investigators will be blinded to treatment assignment; the pharmacy will be unblinded. The SickKids research pharmacist will provide a manual with instructions on how each pharmacy will prepare blinded numbered kits with Mg or 0.9% saline placebo, according to routine IVMg sulfate infusion protocols (**Section 6.4.3 Logistics of Blinding and Kit Making)**. Each site will receive requirements for drug accountability and handling. Unblinding is unlikely and did not occur in MAGNUM. The active Mg and saline placebo are identical in volume, color, odor, and appearance. Further, children with unstable airway will be excluded and only 6% experience a mean BP drop 5mmHg after IVMg with fewer requiring intervention.10

Administration of open-label IV-Mg would highly increase the probability of study contamination and will be strongly discouraged until after 120 minutes after the start of the experimental therapy. Children not responding to/worsening after the experimental therapy will be given back-to-back administration of inhaled salbutamol, other required medications and supplemental oxygen if necessary. In the highly exceptional event of impending respiratory failure after the intervention (children with unstable airway on arrival will be excluded), immediate open-label IVMg will be permitted with locally used Mg doses, but unblinding will not be needed because a 2nd Mg infusion is safe for normotensive patients.47-49,51,60 (**Section**

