**9.3. Secondary outcome measures**

The two study groups will also be compared with respect to:

1. Hospitalization for asthma at the index ED visit.
2. Changes in PRAM, respiratory rate, heart rate, oxygen saturation and blood pressure from baseline (pre- intervention) to 30, 60, 120, and 180 min and also in blood pressure to 10 and 20 min post-intervention
3. Area under the receiver operating characteristic curve for the PRAM score changes at 30, 60, and 120 minutes.
4. PRAM denoting mild asthma (≤ 3 points is a widely accepted discharge criterion25) at 120 minutes
5. Hospitalization for asthma at any medical facility within 72 hours post- ED discharge.
6. Unscheduled asthma-related visits to any health care provider within 72 hours post- ED discharge.
7. Hospital length of stay.
8. Open label IVMg administration after the 120-minute measurement of the primary outcome.

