**9.7. Secondary outcomes**

For the continuous outcomes changes in the PRAM, respiratory rate, heart rate and oxygen saturation from pre-intervention to 30, 60, 120, and 180 min, a mixed model repeated measures will be conducted with treatment group as the between factor (IVMg vs placebo) and the within factor time 0,60,120,180 min. The analysis will be repeated with the randomization stratification factors site and age. Similarly, blood pressure will be analyzed with the additional time measures at 10, 20 and 30 minutes. For overall hospital stay, the study groups will be compared using the Wilcoxon ranked-sum test. For binary outcomes (hospitalization, PRAM indicating mild asthma, unscheduled asthma-related re-visits), groups will be compared using the chi-square test. For the analysis of the area under the ROC curve for PRAM scores, a mixed model repeated measures ANOVA will be conducted with the between factor study group (intervention vs placebo) and within factor time (30, 60, 120 minutes). In addition to the omnibus test for the group and time factors, an orthogonal polynomial analysis will be conducted to compare trends over time between the study groups.

A comparison based on a logistic regression analysis will be conducted adjusting for the randomization stratification factors site and age. As the secondary analyses are exploratory, overall significance for them will be set at 0.05 (2-sided).

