**10.1.**

**Definition of Adverse Events (AE)**

An Adverse Event (AE) is any untoward medical occurrence associated with the use of an intervention in a study participant, which does not necessarily have a causal relationship with the intervention. An AE can therefore be any unfavourable and unintended sign (including an abnormal laboratory finding), symptom or disease temporally associated with the use of the intervention, whether or not considered related to the investigational intervention. Stable chronic conditions which are present prior to entry in the study and do not worsen are not considered AE. These pre-existing conditions will be documented in the participant’s medical history.

A qualified physician, who is part of the study team, will be responsible for determining whether an AE is expected or unexpected, and the relationship to the study intervention will be described as unrelated, unlikely to be related, possibly related, probably related, or related, based on the temporal relationship to the administration of the study intervention and the study physician's clinical judgment.

An AE will be considered unexpected if the nature, severity, or frequency of the event is not consistent with the risk information previously described in section

2.3 (Risk/Benefit Assessment - Participant Safety) and Product Monograph for magnesium.

Adverse events will be collected using Common Terminology Criteria for Adverse Events (CTCAE) version 5.0.

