**10.2.**

**Definition of Serious Adverse Events (SAE)**

Version Date: June 25, 2025 (v3.0)

Page **29** of **54**

[figure not shown]

**MAGICIAN** Clinical Trial Protocol

A Serious Adverse Event is any AE that is:

- fatal

•

•

•

•

•

life-threatening

requires or prolongs inpatient hospital stay

results in persistent or significant disability or incapacity a congenital anomaly or birth defect

an important medical event

The term “life-threatening” in the definition of “serious” refers to an AE in which the participant was at risk of death at the time of the event. It does not refer to an AE that hypothetically might have caused death if it were more severe.

Important medical events are those that may not be immediately life threatening but are clearly of major clinical significance. They may jeopardize the participant and may require intervention to prevent one of the other serious outcomes noted above. Examples of such medical events include allergic bronchospasm requiring intensive treatment in an emergency room or at home, blood dyscrasias or convulsions that do not result in inpatient hospitalization, or the development of drug dependency or drug abuse

**Serious Adverse Event (SAE)** will be documented for any incident that consist of:

1. hypotension below the 5th percentile for age requiring medical intervention within 180 minutes of the start of the experimental therapy, or
2. admission to intensive care unit (ICU) at the index ED visit.
3. admission to intensive care unit (ICU) for asthma within 72 hours after being discharged from ED.

These will be reported to the PI, SickKids REB, local REB and the DSMC.

Since hypotension is the only side-effect of IVMg occurring with appreciable frequency, all enrolled patients will be on precautionary frequent blood pressure monitoring as per the study protocol. If the systolic blood pressure drops below 5th percentile for age, treatment will be given as necessary and DSMC will be notified.

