**11.3.**

**Participant Safety**

Magnesium has a theoretical potential for hypotension, hypopnea and heart block,45 but only hypotension has been reported in previous studies. The IVMg RCT of 1109 adults reported 8% hypotension46 but nobody had Mg stopped for hypotension.

Pediatric IVMg trials with Mg doses 75 and 100 mg/kg did not report any hypotension (N=101).15,20 While a review of the PECARN Registry found a median dose 50 mg/kg had a hypotension rate of 6.8%,10 the mean decrease in the systolic pressure was 5 mm Hg, with uncertain clinical significance. No hypotension was observed in 3 pediatric pharmacologic ICU studies of 75 mg/kg IV Mg in children

≤30 kg and 50 mg/kg in those >30 kg followed by 40 mg/kg/hour for 4 hours.47-49 Two of our participating sites routinely use 75 mg/kg IVMg. A literature review of pediatric status asthmaticus confirms lack of IVMg toxicity.50 Nonetheless, blood pressure will be measured at 30 and 60 minutes and hourly to 180 minutes. If the systolic pressure drops below the 5th percentile-for-age,51 necessary treatment such as IV fluids will be given. If the hypotension occurs at either the 10 minute or 20 minute measurement, further experimental infusion will be stopped and blood pressure will be treated according to local practices. Hypotension will be defined as systolic blood pressure

<70 mm Hg +(age in years x2) in children 2-10 years old and as <90 mm Hg in those >10 years old. Because the children with unstable airway will be excluded and further inhaled salbutamol will be given if needed, lack of Mg in the placebo group will not endanger these participants. All study patients will be monitored for 180 minutes post-intervention prior to discharge, to ensure safety. Only13/723(1.8%) children discharged post IVMg return to the ED vs 1383/38,623(3.6%) without; IVMg is not associated with re-visits.10

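### The only named hypotension outcome counts a low systolic pressure only if it was treated, and no by-arm incidence of low readings is fixed

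*Protocol*

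**What the plan says.** Blood pressure is scheduled in every child at baseline and at 10, 20, 30, 60, 120 and 180 minutes (protocol 1.2, 1.3 and 3). The protocol fixes these uses of the readings:

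- Section 9.4 names a "safety outcome of actionable hypotension (systolic blood pressure <5th percentile for age51 treated with IV fluids/other therapy").
- Section 10.2 lists as a serious adverse event "hypotension below the 5th percentile for age requiring medical intervention within 180 minutes of the start of the experimental therapy".
- Section 9.3 compares changes from baseline, "also in blood pressure to 10 and 20 min post-intervention". Section 9.7 puts them in a repeated-measures mixed model: "Similarly, blood pressure will be analyzed with the additional time measures at 10, 20 and 30 minutes".

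Other passages bear on what is captured:

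- Section 10.1 defines an adverse event widely: "An AE can therefore be any unfavourable and unintended sign (including an abnormal laboratory finding), symptom or disease temporally associated with the use of the" […]. Grade 1 in 10.3.1 covers findings that need no intervention, 10.3.4 has events documented to 3 days, and 9.9 reports frequencies by group.
- Section 10.2 has the DSMC notified when systolic pressure falls below the 5th percentile.
- Section 11.3 says: "If the hypotension occurs at either the 10 minute or 20 minute measurement, further experimental infusion will be stopped". The same sentence goes on to have the pressure treated by local practice. Sections 7.1 and 7.2 tie stopping to hypotension that needs treatment.
- On how often treatment is needed, section 6.5 says "only 6% experience a mean BP drop 5mmHg after IVMg with fewer requiring intervention" and gives no share.

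**The concern.** Hypotension is the one magnesium harm that sections 2.3 and 10.3.3 describe as reported with any frequency, and section 6.2 places the study dose at the upper end of the recommended range. A reader will look to the hypotension count for the safety result. That count requires two things: a low reading and a decision to treat it. The second is left to the clinician (as necessary in 10.2, by local practice in 11.3), and sites also differ on giving a fluid bolus before the infusion (6.1). Section 9.2 rejects hospitalization as the primary outcome because it is a subjective decision shaped by policy and risk tolerance. Similar reasoning applies here.

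The change-from-baseline model does not fill the gap, because it estimates an average shift and not the number of children who fell below a threshold. The trial could report few treated episodes while its own readings contain more low pressures, with no planned table showing the difference.

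**Working it through.** The protocol states no expected count or power for hypotension, so there is no figure of its own to reproduce. The check has two parts.

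**1. Which records count an episode?**

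| Episode | 9.4 outcome | 10.2 hypotension item | 9.3/9.7 model | Ordinary adverse event (10.1, 9.9) |
|---|---|---|---|---|
| Below 5th percentile, treated | Yes | Yes, if the treatment was required | Mean change only | Yes |
| Below 5th percentile, infusion stopped, nothing else given | Unclear: the text does not say whether a stop is other therapy | Unclear, same reason | Mean change only | If entered |
| Below 5th percentile, no action | No | No | Mean change only | If entered |

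No passage says that every sub-threshold reading must be entered as an adverse event. The DSMC notice in 10.2 is triggered by the reading itself, but it is oversight and not a by-arm result.

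The threshold also varies. Sections 7.2, 9.4 and 10.2 use the 5th percentile for age. Sections 6.6, 7.1 and 11.3 use a mm Hg formula (below 70 + 2 × age at 2–10 years, below 90 above 10 years). Section 10.3.3 adds a further conflict: it says the monograph events other than flushing and sweating, hypotension among them, mandate ICU admission and so are serious. Section 10.2 makes hypotension serious when it requires intervention.

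**2. How far can the named count fall below the number of hypotensive children?**

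Inputs:
- 96 children per arm (9.1).
- Hypotension rate r = 6.8% from the registry (2.3, 11.3), with 8% from the adult trial (2.3) as an alternative.
- Treated share f, which the documents do not give. It is assumed here over 10% to 100%.

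Formulas, taking children as independent:
- Hypotensive children in the magnesium arm = 96 × r.
- Expected 9.4 events = 96 × r × f.
- Chance of no 9.4 event = (1 − r × f)^96.

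At r = 6.8%, 96 × 0.068 = 6.5 children. At r = 8%, 96 × 0.08 = 7.7.

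| f | Events, r = 6.8% | Chance of none | Events, r = 8% | Chance of none |
|---|---|---|---|---|
| 10% | 0.7 | 52% | 0.8 | 46% |
| 25% | 1.6 | 19% | 1.9 | 14% |
| 50% | 3.3 | 4% | 3.8 | 2% |
| 75% | 4.9 | 0.7% | 5.8 | 0.3% |
| 100% | 6.5 | 0.1% | 7.7 | <0.1% |

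For example, at r = 6.8% and f = 10%: (1 − 0.0068)^96 = 0.519.

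**The case against.** The strongest reply is that untreated hypotension is not lost. The adverse event definition has no treatment condition, grade 1 fits an untreated low reading, events are documented to 3 days and tabulated by group, and the DSMC hears of any fall below the 5th percentile. This stands as far as it goes. A reader might infer that most hypotension would go unreported, and the documents do not support that. *Unreported* ignores these routes. *Most* would need a treated share below 50%, and the protocol says only that fewer need intervention. What remains is that the adverse event route depends on someone entering the reading.

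A reader might also infer that episodes ending in a stopped infusion are excluded from the count. The text does not establish this. Section 11.3 pairs the stop with treatment by local practice, and 7.1 and 7.2 stop for hypotension that needs treatment, so many stopped infusions would count. Only a stop with nothing else given is unresolved.

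The background rate is uncertain too. The 6.8% comes from a registry with a median dose of 50 mg/kg, while section 2.3 reports no hypotension in pediatric trials at 75 and 100 mg/kg (N = 101). If the true rate is near zero, both counts are near zero.

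Nor does the treatment condition by itself bias the comparison between arms: clinicians are blinded and randomization is stratified by site (6.5). It thins the count and blurs what is counted.

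Finally, section 9.4 says these outcomes cannot be powered, and the form of a safety table can be left to an analysis plan. Both are fair. But 9.4 itself fixes the outcome and its treatment condition, so that choice is not left open.

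**Conclusion.** The point holds in a limited form. The one named hypotension outcome and the 10.2 hypotension item depend on treatment given or required, and the protocol fixes no by-arm incidence of low systolic pressure, although it schedules the readings needed. At the cited 6.8%, about 6.5 of 96 magnesium children would be hypotensive. The 9.4 count could be anywhere from 0.7 to 6.5, with a chance of none from 52% down to 0.1%, as the treated share runs from 10% to 100%. This rests on the registry rate carrying over to this trial and on an assumed treated share. It shows how wide the gap could be, not how wide it will be. The two thresholds and the differing stop and serious-event wording are contradictions in the text whatever the rate.

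**What to change.** First, reconcile the two definitions of hypotension (5th percentile in 7.2, 9.4 and 10.2; mm Hg formula in 6.6, 7.1 and 11.3) and the stop and serious-event wording in 7.1, 7.2, 10.2, 10.3.3 and 11.3. Which definition or rule applies is for the investigators; this review does not choose. State also whether stopping the infusion counts as other therapy in 9.4.

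Then keep actionable hypotension in 9.4 and add the proportion of children in each arm with at least one systolic reading below the single stated threshold from 10 to 180 minutes, treated or not, with the risk difference and a confidence interval. List separately the infusions stopped for hypotension and the hypotension that was treated.

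The cost is a few lines in 9.4 and 9.9, the reconciling edits, and one derived variable. There is no new measurement and no change to the sample size. The downside is a higher reported hypotension rate that will include some readings of uncertain clinical importance; listing treated episodes and stopped infusions separately lets the reader judge that.

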**9.5. Analyses: Primary efficacy analysis**

We will adopt an intention-to-treat (ITT) approach and a sensitivity analysis using a per- protocol (PP) approach. Variables will be reported using frequencies and proportions; and continuous variables will be expressed as means and standard deviations or medians and interquartile ranges in case of non-normal distribution. Baseline variables will be compared between the IVMg vs placebo using standardized differences (SD) with an absolute SD < 0.10 being considered balanced.

Version Date: June 25, 2025 (v3.0)

Page **26** of **54**

[figure not shown]

**MAGICIAN** Clinical Trial Protocol

**9.6. Primary outcome**

For the primary outcome of the change in PRAM at 120 minutes, the study groups will be compared using the Student’s t-test. A comparison based on a multiple regression analysis will be conducted adjusting for the randomization stratification factors site and age.

**9.7. Secondary outcomes**

For the continuous outcomes changes in the PRAM, respiratory rate, heart rate and oxygen saturation from pre-intervention to 30, 60, 120, and 180 min, a mixed model repeated measures will be conducted with treatment group as the between factor (IVMg vs placebo) and the within factor time 0,60,120,180 min. The analysis will be repeated with the randomization stratification factors site and age. Similarly, blood pressure will be analyzed with the additional time measures at 10, 20 and 30 minutes. For overall hospital stay, the study groups will be compared using the Wilcoxon ranked-sum test. For binary outcomes (hospitalization, PRAM indicating mild asthma, unscheduled asthma-related re-visits), groups will be compared using the chi-square test. For the analysis of the area under the ROC curve for PRAM scores, a mixed model repeated measures ANOVA will be conducted with the between factor study group (intervention vs placebo) and within factor time (30, 60, 120 minutes). In addition to the omnibus test for the group and time factors, an orthogonal polynomial analysis will be conducted to compare trends over time between the study groups.

A comparison based on a logistic regression analysis will be conducted adjusting for the randomization stratification factors site and age. As the secondary analyses are exploratory, overall significance for them will be set at 0.05 (2-sided).

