**9.12.**

**Economic analysis**

We will assess the cost-effectiveness of IVMg to alleviate respiratory distress. We will use cost-utility analysis (CUA) to assess the incremental cost-effectiveness of IVMg vs placebo in terms of cost per quality-adjusted life year and cost-effectiveness analysis to assess cost per alleviating respiratory distress (PRAM ≤3). Using a decision tree, analyses will be undertaken from the perspective of the Canadian healthcare system over a 72-hour horizon which will conform to Canadian guidelines for economic evaluation.74

Comparative effectiveness of IVMg versus placebo will be derived from the MAGICIAN data, including PRAM ≤3 points at 3 hours (secondary outcome c); patient disposition (i.e., discharge or hospitalization during the index ED visit; secondary outcome a), resource use (secondary outcomes d–f), and adverse events. Costs will include drug acquisition and administration, healthcare resource use, and adverse event management. For the CUA, utilities will be sourced from the literature. Scenario analyses will include adopting a societal perspective. Further information can be found in Appendix E: Economic Analysis.

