**APPENDIX E - Economic analysis**

The cost-effectiveness of IVMg versus placebo to alleviate respiratory distress will be assessed from the perspective of the Canadian public health care system. To this end, trial-based cost- utility analysis (CUA) and cost-effectiveness analyses (CEA) will be conducted, using a decision-tree framework. First, CUA will be performed, in which costs and quality-adjusted life years (QALYs) associated with each treatment will be estimated, and the incremental cost per QALY gained will be determined. Second, a CEA will be used to assess the incremental cost per alleviating respiratory distress (i.e., achieving mild asthma status indicated by PRAM ≤ 3 points). Although the MCID for PRAM in the MAGICIAN trial is a change of at least 1 point, the decision problem will focus on the alleviation of respiratory distress (PRAM ≤ 3 points) as signifies dischargable mild asthma. Both analyses will be conducted over a 72-hour horizon, given that all costs and benefits of IVMg treatment are expected to be experienced within 72 hours. In the CUA, the accumulated QALYs for both treatments are expected to be small owing to the 72-hour time frame; however, the cost-effectiveness of IVMg will be informed by the incremental difference in QALYs (as part of the incremental cost-utility ratio calculation). All analyses will adhere to the Guidelines for the Economic Evaluation of Health Technologies: Canada (CADTH 2017; 4th edition).

Comparative effectiveness of IVMg versus placebo will be derived from the MAGICIAN trial. Treatment response (PRAM indicating mild asthma [≤3 points]; secondary outcome c) will be assessed at 180 minutes. Patient disposition (i.e., discharge or admission to hospital for asthma) during the index ED visit; secondary outcome a), resource use (secondary outcomes d, e, f), and adverse events will additionally be obtained from the MAGICIAN trial. To determine costs, a unit cost will be applied to each type of resource, and the total cost will be estimated as the weighted sum of resource use (the sum of the product of the number of each resource item and its unit cost). Costs associated with AEs will be based on the observed frequency of each AE in the MAGICIAN trial and costs associated with their management. The resources, type of measurement, and source of the cost data are described in the following table:

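### The repeated-measures time factor in 9.7 omits 30 minutes and includes time 0 for change outcomes, and the economic response is labelled as a trial outcome that is defined an hour earlier

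*Protocol*

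**What the plan says.** **Continuous secondary outcomes.** Protocol 9.3, item 2, lists changes in PRAM and vital signs, including "oxygen saturation and blood pressure from baseline (pre- intervention) to 30, 60, 120, and 180 min", with 10 and 20 minutes added for blood pressure. The secondary endpoints in Section 3 give 30, 60, 120 and 180 minutes for PRAM, oxygen saturation, heart rate and respiratory rate. Section 9.7 repeats these times for the outcome: "oxygen saturation from pre-intervention to 30, 60, 120, and 180 min, a mixed model repeated measures will be conducted". The same sentence then sets up the model "with treatment group as the between factor (IVMg vs placebo) and the within factor time 0,60,120,180 min". The next sentence on timing reads "Similarly, blood pressure will be analyzed with the additional time measures at 10, 20 and 30 minutes".

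**Mild-asthma response.** In 9.3 the fourth item is "PRAM denoting mild asthma (≤ 3 points is a widely accepted discharge criterion25) at 120 minutes". Question d of Section 3 gives the same time. The economic analysis in 9.12 takes its effectiveness inputs from the trial, "including PRAM ≤3 points at 3 hours (secondary outcome c", and Appendix E states "secondary outcome c) will be assessed at 180 minutes". Both places refer to resource use as secondary outcomes d to f.

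**The concern.** The two halves of one sentence in 9.7 do not agree. The outcomes are defined at 30, 60, 120 and 180 minutes; the factor that indexes them has 0 in place of 30. An analyst who follows the factor drops the reading taken at the end of the infusion for three vital signs and from the main PRAM model. An analyst who also follows the word change enters a level at which nothing can vary.

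The economic sections name a trial secondary outcome but give it a different time and a letter that belongs to another outcome. A reader could not tell whether the cost-effectiveness ratio rests on the 120-minute outcome or on a 180-minute response that the outcome lists do not contain. The resource-use letters have the same fault and, read literally, leave out hospital length of stay.

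**Working it through.** The plan states no figure on this point, so there is none to reproduce. The check compares the text and adds some short algebra.

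**1. Is 30 minutes really left out?**
- Outcome times in 9.3, in the Section 3 endpoints and in the first half of the 9.7 sentence: 30, 60, 120, 180.
- Levels of the time factor in 9.7: 0, 60, 120, 180.
- The blood-pressure sentence lists 30 minutes among the times to be added, so 30 is not in the base factor. The omission is not shorthand.
- The Section 1.2 schema schedules all these measurements at 30 minutes, so the data will exist.

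**2. What does time 0 do if change is modelled?**
Write d60, d120 and d180 for the between-group differences in change. At time 0 each child's change is baseline minus baseline = 0, so the group difference there is 0. The equal-weight group main effect is

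(0 + d60 + d120 + d180)/4 = 3/4 × (d60 + d120 + d180)/3.

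The factor 3/4 holds for any pattern of effects. As an illustration, assume a difference of 1.0 point at every time after the start:
- levels 0, 60, 120, 180: (0 + 1 + 1 + 1)/4 = 0.75
- levels 30, 60, 120, 180: (1 + 1 + 1 + 1)/4 = 1.00

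For blood pressure, if the base factor with time 0 is carried over, the levels are 0, 10, 20, 30, 60, 120 and 180, and the factor is 6/7 = 0.86.

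The row and column for time 0 in the 4 × 4 covariance matrix of the changes are all zero. With SD 2.5 and correlations of 0.3, 0.5 and 0.7 among the other three times, the rank is 3 and the determinant is 0 in each case. An unstructured covariance would therefore be singular.

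The contrast at 120 minutes alone is still d120, whichever levels are listed.

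**3. Which outcome is c?**
- Section 3: c is the ROC area, d is PRAM ≤3 at 120 minutes, e is the subgroup question, f is hospitalization within 72 hours, g is unscheduled visits, h is length of stay.
- Section 9.3, counting items as letters: c is the ROC area, d is PRAM ≤3 at 120 minutes, e is hospitalization within 72 hours, f is unscheduled visits, g is length of stay.
- Under 9.3, d to f leaves out length of stay. Under Section 3, d to f leaves out both unscheduled visits and length of stay. Under either list it wrongly takes in PRAM ≤3.
- If the ROC item is struck from the 9.3 list, c becomes PRAM ≤3, and d to f become 72-hour hospitalization, unscheduled visits and length of stay. This is what the economic sections evidently intend.

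**The case against.** **Raw scores.** A time factor with 0 as a level is ordinary when observed scores are modelled. Change from baseline is then a group-by-time contrast, time 0 has normal variance and nothing is singular. This stands as an alternative: the protocol does not say plainly which response is modelled, although the sentence speaks of changes. It does not restore 30 minutes.

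**Hourly changes.** Question b of Section 3 asks about hourly changes to 180 minutes, which fits a 0, 60, 120, 180 grid. The document is therefore divided, but 9.3, the endpoint list and the 9.7 sentence itself all include 30.

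**30 minutes appears elsewhere.** Section 9.7 analyses PRAM at 30, 60 and 120 minutes under the ROC outcome and adds 30 minutes for blood pressure. So the time point is lost entirely only for respiratory rate, heart rate and oxygen saturation.

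**An economic analysis may choose its own time.** It may. PRAM is scheduled at 180 minutes, 9.12 and Appendix E agree with each other, and later treatment can be counted as part of each strategy. The defect is presenting this response as a trial outcome that is defined at 120 minutes.

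**Stronger readings that a reader might infer.** One is that the model must fail or must understate the effect by 25%. Failure needs change scores, time 0 as a level and an unstructured covariance, and 9.7 names no covariance structure. The 25% applies only to an equal-weight main effect on change scores. Another is that rescue magnesium dilutes the 180-minute response by about a quarter, because 215/816 (26.3%) children in the nebulized-magnesium trial received IV magnesium (Appendix C). That figure covers both nebulized arms at any time after inhaled therapy. It says nothing about placebo children between 120 and 180 minutes here, so no numerical dilution can be claimed.

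**Conclusion.** Section 9.7 is wrong as written: its time factor does not match its outcomes, and 30 minutes is dropped from the main model. If change scores are modelled, the time-averaged group effect on an equal-weight basis is 3/4 of the average at 60, 120 and 180 minutes, and one level has no variance. If raw scores are modelled, time 0 is legitimate and only the missing 30-minute level remains.

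The economic response carries the wrong time or the wrong label, and the resource-use letters point to the wrong items. This looks like a renumbering slip.

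The impact is moderate. The protocol calls the secondary analyses exploratory, and neither the primary comparison at 120 minutes nor any contrast at a single modelled time is affected.

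**What to change.** **Section 9.7.** State whether the response is change or raw score.
- If change: use levels 30, 60, 120 and 180 minutes (plus 10 and 20 for blood pressure), with the baseline value as covariate, and report arm differences at each time.
- If raw score with time 0 as a level: add 30 minutes and take the treatment effect from the group-by-time contrasts. The group main effect should not be used, because it averages in a pre-treatment level.

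Reconcile the hourly wording of question b with the 30-minute endpoint.

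**Section 9.12 and Appendix E.** Either use PRAM ≤3 at 120 minutes, or define the 180-minute response as a separate economic outcome with 120 minutes as a sensitivity analysis. If 180 minutes is kept, note that Section 6.3 discourages open-label magnesium only until 120 minutes and that 9.3 counts later use as an outcome in itself: "Open label IVMg administration after the 120-minute measurement of the primary outcome". Correct the letters so that the resource-use items are 72-hour hospitalization, unscheduled visits and length of stay.

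**Cost.** Wording only, best done before unblinding. All the readings are already scheduled and no new data are needed. If the 120-minute response is chosen, the economic base case moves one hour earlier.
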